## Abstract

**Background:**

Myofascial pain remains an underdiagnosed contributor to musculoskeletal pain conditions, including plantar heel pain, which is the most common source of foot pain. The current standard for diagnosing myofascial pain is a clinical examination using manual palpation. However, this approach lacks quantitative thresholds for precise assessment of myofascial pain, highlighting the need for validated biomarkers.

**Objective:**

This protocol describes the development of a diagnostic imaging biosignature of myofascial pain using both ultrasound and magnetic resonance imaging to differentiate individuals with plantar heel pain from those with other kinds of foot pain and matched pain-free controls. The study will also explore whether diagnostic accuracy is enhanced by creating a composite biosignature that includes psychological factors.

**Methods:**

In this cross-sectional study, 100 participants will be recruited: 50 with plantar heel pain, 25 with insertional Achilles tendinopathy, and 25 pain-free controls. Participants will undergo a clinical examination of 5 calf and foot muscles to identify sites of abnormal myofascial tissue. The primary imaging outcomes will capture biochemical properties (T1ρ of muscle and fascia), biomechanical properties (shear wave speed of the muscle, shear strain of the plantar fascia during passive movement), and structural profile (fat fraction of the muscle, thickness of the plantar fascia). Patient-reported outcomes will include the National Institutes of Health’s Helping to End Addiction Long-term (HEAL) Initiative Common Data Elements and additional psychological measures.

**Results:**

This study is supported by grant R61AT012275 from the National Center for Complementary and Integrative Health and the National Institute of Neurological Disorders and Stroke, awarded in September 2024. Participant enrollment began in May 2025. As of November 2025, a total of 55 participants have been enrolled. Enrollment is expected to conclude no later than July 2026. The anticipated study completion date is August 2026. Data will be shared within 1 year of completing the study or upon publication, whichever occurs first.

**Conclusions:**

This protocol provides novel mechanistic insight into myofascial pain through advanced imaging techniques, offering a biopsychosocial framework for improving the diagnosis and treatment of plantar heel pain and related conditions. We anticipate that combining imaging and psychosocial measures will improve the diagnostic accuracy of the biosignature and provide a more comprehensive understanding of myofascial pain.

**Trial Registration:**

ClinicalTrials.gov NCT06803056; https://clinicaltrials.gov/study/NCT06803056; OSF Registries osf.io/nxqfj; https://osf.io/nxqfj

**International Registered Report Identifier (IRRID):**

DERR1-10.2196/87613

## Introduction

Plantar heel pain, the most common source of foot pain, affects approximately 1 out of every 10 adults and accounts for approximately 2 million medical visits annually in the United States [1,2]. Individuals with plantar heel pain frequently experience reduced quality of life and diminished satisfaction with activities of daily living [3,4]. Plantar heel pain is characterized by pain along the sole, most noticeable during initial steps following a period of inactivity and during prolonged weight-bearing activities [5]. The term “plantar fasciitis” is often used to describe this condition and suggests inflammation as the main cause of heel pain. However, the broader term “plantar heel pain” is preferred, reflecting the multifactorial nature of the underlying causes—including myofascial changes, adjacent tissue pathology, and psychosocial factors [5-9].

One potentially underrecognized component of plantar heel pain is myofascial pain, which is characterized by the presence of trigger points in the calf and foot muscles that can reproduce the individual’s pain [10,11]. Trigger points are defined as hypersensitive areas within a tight band of skeletal muscle that elicit local or referred pain when compressed, contracted, or stretched. The current standard for diagnosing myofascial pain relies on a clinical examination using manual palpation [12,13], which lacks objectivity and quantitative precision. Identifying a diagnostic imaging biomarker [14] for trigger points could significantly improve the accuracy of diagnosing myofascial pain and inform targeted treatment strategies.

Imaging is a powerful, yet underused, diagnostic tool that can be used to identify muscles with trigger points [15]. Ultrasound and magnetic resonance imaging (MRI) are both commonly used clinically to evaluate soft tissues [16-18]. Ultrasound is a noninvasive imaging technique with minimal contraindications that provides real-time assessments of soft tissue, including muscles and fascia [19]. In particular, ultrasound shear wave elastography (SWE) demonstrates high diagnostic accuracy in capturing abnormal biomechanical properties of myofascial tissue [15]. MRI is often regarded as the gold standard for evaluating soft tissues due to its ability to provide superior contrast, high resolution, and multiplanar images [18]. Previous studies have shown promise using T1 signal intensity and T2 mapping to detect structural alterations in trapezius muscles in women with migraines [20-22]. To build on previous foundational work, further research is needed to examine the diagnostic capabilities of both ultrasound and MRI within the same sample and to expand imaging approaches for identifying trigger points in the foot and ankle.

The primary aim of this proposed study is to develop a diagnostic imaging biosignature of myofascial pain to differentiate individuals with plantar heel pain from those with other kinds of foot pain (specifically insertional Achilles tendinopathy) and from matched pain-free controls. We hypothesize that a diagnostic biosignature, which uses both advanced ultrasound and MRI to quantify biochemical (muscle and fascia T1ρ), biomechanical (muscle SWE and fascia strain), and structural (muscle fat fraction and fascia thickness) tissue properties, will more accurately identify myofascial pain in the foot and ankle than a single imaging biomarker alone. We will also explore the potential of composite biosignatures that combine multiple imaging biomarkers with psychological factors, such as kinesiophobia, to provide a more comprehensive assessment. The development of a diagnostic biosignature may provide novel mechanistic insights into myofascial pain and offer a framework to facilitate the diagnosis of myofascial pain contributing to plantar heel pain.

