### Statistical Analysis

#### Data Analysis

In the statistical analysis, quantitative measures will be summarized with means, SDs, and quantiles, and categorical measures, including the presence of trigger points (trigger points vs healthy tissue), will be summarized with counts and percentages. Data will be described for 3 calf muscles (medial gastrocnemius, lateral gastrocnemius, and medial soleus) and 2 foot muscles (abductor hallucis and flexor digitorum brevis).

The primary study aim is to examine the diagnostic performance of 20 candidate biomarkers (biomechanical, biochemical, and structural) in distinguishing between tissue with and without myofascial pain. Performance will be quantified with the area under the receiver operating characteristic curve (ROC AUC), pooled over the 5 muscle groups assessed on each participant for imaged metrics and trigger points. Five-fold cross-validation will be used to estimate predictive performance, and bootstrap resampling applied to obtain 95% CIs. Participants will be treated as the sampling units in cluster cross-validation and bootstrap sampling algorithms to account for repeated muscle measurements in each participant. To identify the most promising biomarkers and account for multiple comparisons, false discovery rates will be computed with the method of Benjamini and Hochberg to rank the biomarkers in order of diagnostic performance [73]. Up to 5 top-performing biomarkers will be selected to constitute a single biosignature to achieve a target AUC >0.7, sensitivity >60%, and specificity >60%.

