#### Sample Size

The target sample size of 50 individuals with plantar heel pain, 25 individuals with insertional Achilles tendinopathy, and 25 pain-free controls was chosen to provide a 95% CI half-width of 0.10 for an AUC of 0.70. This calculation assumes 5 muscle measurements for each participant, an intraclass correlation coefficient of 0.5 among them, and an overall active trigger point prevalence of 36% in individuals with plantar heel pain [10,74]. Further assuming that the 20 candidate biomarkers have AUCs uniformly distributed from 0.5 to 0.8, the study will have at least 85% power to obtain a biosignature meeting the desired AUC threshold.

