### Conclusions

This protocol provides novel mechanistic insights into myofascial pain through advanced imaging, offering a biopsychosocial framework for improved diagnosis and treatment of plantar heel pain and related conditions. We anticipate that combining imaging and psychosocial measures will improve the diagnostic accuracy of the biosignature and provide a more comprehensive understanding of myofascial pain.

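### The hypothesis compares a biosignature with a single biomarker, but the stated target and power are absolute and say almost nothing about that comparison

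*Protocol article*

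**What the plan says.** All references are to the protocol article.

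- **Introduction.** The hypothesis attached to the primary aim is comparative: the combined biosignature "will more accurately identify myofascial pain in the foot and ankle than a single imaging biomarker alone".
- **Data Analysis.** Each of 20 candidate biomarkers gets an ROC AUC, with five-fold cross-validation and bootstrap 95% CIs that take the participant as the sampling unit. The biomarkers are ranked by false discovery rate. Then: "Up to 5 top-performing biomarkers will be selected to constitute a single biosignature to achieve a target AUC >0.7, sensitivity >60%, and specificity >60"%.
- **Data Analysis, exploratory aim.** AUC is estimated for each composite model in the same way, and variable importance is reported. No contrast between models is described.
- **Sample Size.** The study is sized for a 95% CI half-width of 0.10 at an AUC of 0.70. It is further assumed that the "20 candidate biomarkers have AUCs uniformly distributed from 0.5 to 0.8", and on that basis "the study will have at least 85% power to obtain a biosignature meeting the desired AUC threshold".
- **Conclusions.** The authors anticipate that "combining imaging and psychosocial measures will improve the diagnostic accuracy of the biosignature".

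**The concern.** A statement that one thing is more accurate than another needs an estimate of the difference. The article fixes a hypothesis, a target and a power statement, and the last two refer to the biosignature's own AUC only. If single biomarkers are expected to pass 0.7 unaided, a biosignature can meet the target while being no better than its best component.

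The study would then reach its stated goal without a pre-specified result bearing on its hypothesis. That matters for use: a signature needing both ultrasound and an MRI session is worth its burden only if it improves on one measurement.

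**Working it through.** **Inputs from the article.** 20 candidate biomarkers; AUCs uniform on 0.5 to 0.8; target AUC above 0.7 with sensitivity and specificity above 60%; power at least 85%; half-width 0.10 at AUC 0.70; 5 muscles per participant; ICC 0.5; trigger point prevalence 36% in plantar heel pain; groups of 50, 25 and 25.

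**1. The plan's power figure.** The share of single biomarkers with true AUC above 0.7 is (0.8 − 0.7)/(0.8 − 0.5) = 1/3. The chance that at least 5 of 20 exceed 0.7 is P(Bin(20, 1/3) ≥ 5) = 0.8485, which rounds to the stated 85%. The article gives no formula, so the match is an inference. If it is how the figure arose, the 85% describes single biomarkers passing 0.7 and involves no gain from combining them.

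**2. Single biomarkers under the same assumption.**

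- Expected number above 0.7: 20 × 1/3 = 6.7. On an evenly spaced grid the count is 7.
- Chance that at least one exceeds 0.7: 1 − (2/3)^20 = 0.9997.
- Expected AUC of the best one: 0.5 + 0.3 × 20/21 = 0.786.
- Chance that the best *estimated* AUC exceeds 0.7, by simulation with SE = 0.10/1.96 = 0.051 and an assumed correlation of 0 to 0.7 between estimates: 98% to 100%. This largely restates the assumed AUC range.

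**3. The sensitivity and specificity limits.** Under an equal-variance binormal model (my assumption), sensitivity = specificity = Φ(Φ⁻¹(AUC)/√2) at the symmetric cut-off. At AUC 0.70 both are 64.5%. Reaching 60% for both needs only AUC = Φ(√2 × Φ⁻¹(0.60)) = 0.640. A single biomarker above 0.7 would normally meet these limits too.

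**4. The selection rule.** It caps the signature at five and sets no minimum above one. A one-marker signature could meet the target, and it cannot be more accurate than itself.

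**5. What the comparison could show with 100 participants (illustrative).** These assumptions are not in the article: equal-variance binormal markers with equal pairwise correlation; the expected top five AUCs of 0.786, 0.771, 0.757, 0.743 and 0.729; optimal weights; a correlation of 0.5 to 0.7 between the two AUC estimates. Standard errors are Hanley-McNeil with design effect 1 + 4 × 0.5 = 3. Three layouts of sites with and without trigger points are used: 90 v 160 (plantar heel pain only), 90 v 410 (no trigger points in controls) and 180 v 320 (36% in every group).

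With δₖ = √2 × Φ⁻¹(AUCₖ) and marker correlation matrix Σ, the combined AUC is Φ(√(δ′Σ⁻¹δ)/√2). Power is Φ(difference/SE of difference − 1.96).

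| Marker correlation | Combined AUC | Gain over 0.786 | 95% CI half-width of the difference | Power |
|---|---|---|---|---|
| 0 | 0.94 | 0.156 | 0.056–0.094 | 90% or more |
| 0.3 | 0.86 | 0.071 | 0.056–0.101 | 28–71% |
| 0.5 | 0.82 | 0.037 | 0.057–0.105 | 10–24% |
| 0.7 | 0.80 | 0.015 | 0.058–0.107 | 5–7% |

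In every row the combined AUC is well above 0.7, while the gain over one marker runs from 0.015 to 0.156. The threshold does not separate these cases.

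**The case against.** - **The comparison may be planned elsewhere.** Only a journal article is shown, and the form of a contrast between models is often left to the SAP. A reader might infer that the hypothesis is never tested; the article cannot show that. What stands is that its own target and power statement do not address its own hypothesis.
- **Readers could compare the reported AUCs.** All AUCs share one metric and one resampling scheme, so an informal comparison is possible. But separate intervals with half-widths near 0.10 do not give the paired difference within the same participants, and the best of 20 estimates is optimistic unless it is chosen inside the training folds.
- **No rule equates the target with the hypothesis.** A reader might infer that the study would declare its hypothesis confirmed at AUC 0.7. The article calls this a target for a signature under development and says no such thing. The point is that nothing else is offered for judging the hypothesis.
- **The hypothesis does not say best.** It refers to a single imaging biomarker. The best one is the strictest comparator and is my choice, because beating a weak marker would not justify combining several.
- **The psychological composite is exploratory.** The Conclusions state an expectation, not a confirmatory claim. This objection stands: a descriptive contrast is enough there.

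**Conclusion.** The mismatch is real and should be fixed. Under the article's own assumption, about 7 of 20 single biomarkers exceed 0.7 and at least one does so with probability 0.9997. Meeting the AUC, sensitivity and specificity target is therefore almost uninformative about added value. That conclusion rests on the assumed uniform distribution of AUCs, which is a planning assumption and not a result, and on the binormal model for the sensitivity and specificity limits.

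Three stronger readings are not supported:

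- **That the 85% power is wrong, or ignores the sample size.** It reproduces, but by an inferred route.
- **That the 0.10 half-width is wrong.** It comes out at 0.112 with trigger points in the plantar heel pain group only and 0.086 with 36% in every group. It equals 0.10 at an overall prevalence of 23.5%, about 11% in controls, which is plausible.
- **That the study is too small for the comparison.** This turns on the marker correlation, which the article does not give.

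**What to change.** 1. Pre-specify, as the estimate for the hypothesis, the paired difference in cross-validated AUC: biosignature minus best single biomarker. Select both within the same training folds, and give a participant-cluster bootstrap 95% CI.
2. State the expected precision of that difference over a range of marker correlations, and acknowledge that power may be low if the markers are correlated.
3. Keep the AUC, sensitivity and specificity target as a separate performance goal.
4. For the psychological composite, report the same paired difference against the imaging-only model descriptively, without a pass/fail rule.

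The alternative to items 1 and 2 is to reword the hypothesis so that it claims only what the threshold target can show.

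The cost is SAP wording and a few lines of code on resamples already planned. No data collection changes, and with enrolment expected to end by July 2026 the change can precede the final analysis. The downside is that the comparative claim becomes harder to support, and the interval may be too wide to settle it.

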## Methods

### Participants

This cross-sectional study will enroll a total of 100 participants, including 50 individuals diagnosed with plantar heel pain, along with 2 control groups. The first control group will consist of 25 individuals with insertional Achilles tendinopathy, for whom targeted myofascial treatments are not considered first-line interventions [23]. The second control group will include 25 pain-free individuals with a similar age, BMI, and sex distribution as the plantar heel pain and insertional Achilles tendinopathy groups. To ensure balanced representation, enrollment will be structured so that neither sex comprises more than 60% of each group. Eligibility and group assignment will be based on the inclusion and exclusion criteria outlined in Textbox 1. Screening for study eligibility will occur in three phases: (1) an online screening form, (2) a video visit with a physical therapist, and (3) an in-person clinical examination by a physical therapist. Individuals who provide informed consent and meet all criteria will be enrolled in this study.

Eligibility criteria.
**Inclusion criteria**
For the plantar heel pain and insertional Achilles tendinopathy group:Clinical diagnosis of plantar heel pain [5] or insertional Achilles tendinopathy [23].Duration of pain ≥3 months.Severity of pain ≥3/10.
**Exclusion criteria**
For all groups:Age <18 years.History of invasive procedures to the foot or ankle on the side of interest.History of lower extremity injections, dry needling, extracorporeal pulse activation treatment, or extracorporeal shockwave therapy within the past 3 months on the side of interest.Contraindications for MRI (eg, non–magnetic resonance–compatible implanted devices, claustrophobia, inability to remain still comfortably for 1 hour in a supine position [24])Clinically unstable medical or psychiatric issues.Comorbidities associated with changes in musculoskeletal imaging, including rheumatologic and inflammatory conditions that directly impact the musculoskeletal system (eg, rheumatoid arthritis, spondyloarthropathy, and gout), osteoarthritis of the foot or ankle, diabetes, neuromuscular diseases (eg, Charcot-Marie-Tooth [CMT] disease), familial hypercholesterolemia, history of foot or ankle fracture, neoplasms involving the foot, plantar fibromatosis, or recent (within the past 1 year) infection of the foot or ankle (eg, infectious fasciitis and calcaneal osteomyelitis).For the plantar heel pain and insertional Achilles tendinopathy group:Other sources of heel pain (eg, tarsal tunnel syndrome, peripheral neuropathy, lumbar radiculopathy, calcaneal stress fracture, fibromyalgia, Morton’s neuroma, or Baxter neuropathy).Additional exclusion criteria for insertional Achilles tendinopathy group: co-occurring plantar heel pain and Achilles tendinopathy.For the pain-free control group:Persistent or recurrent leg pain in the past 6 months.

### Data Collection Procedures

#### Overview

This cross-sectional study will include 3 main components of data collection: a clinical evaluation, ultrasound imaging, and MRI (Figure 1).

**Figure 1 figure1:**
[figure not shown]
Study flow diagram. This diagram outlines the sequential study procedures, starting with participant recruitment, consent, and eligibility assessment. It proceeds through a clinical examination of the calf and foot muscles to identify trigger points. Following the clinical assessment, participants undergo ultrasound and magnetic resonance imaging (MRI) with minimal delay to ensure spatial correspondence of identified trigger points across imaging modalities. The entire study visit lasts approximately 3 hours in a single session. MR: magnetic resonance; US: ultrasound.

#### Clinical Examination

The clinical examination will be performed by a physical therapist with advanced training in dry needling for myofascial pain and will include (1) movement tasks, (2) trigger point identification, and (3) pressure pain threshold testing. In addition, participants will complete a series of patient-reported outcome measures. These outcomes align with the HEAL Common Data Elements and are supplemented by additional psychological surveys, as well as foot- and ankle-specific pain and function outcomes [25] (Table 1).

**Table 1 table1:** Patient-reported outcome measures.

Outcome							Description		Psychometrics
**Pain**									
		PEG^a^				A 3-item instrument that evaluates pain intensity and its impact on enjoyment and general activity. Each item is scored from 0 to 10, and the 3 scores are averaged to yield a total PEG score, with higher values indicating greater pain and interference [26].		Internal consistency: Cronbach α=0.73 Validity: r=0.60-0.89 (in chronic musculoskeletal pain populations)	
	PROMIS^b^-Pain Interference Short Form				Assesses pain interference, which quantifies the self-reported impact of pain on social, cognitive, emotional, physical, and recreational domains. This instrument yields raw scores from 6 to 30, based on 6 items scored from 1 (“not at all”) to 5 (“very much”). Scores are converted to T-scores (mean 50, SD 10; range ~30 to over 80) standardized to the US general population. T-scores below 55 are within normal limits, 55-60 suggest mild, 60-70 moderate interference, and scores >70 reflect severe interference [27-29].				Internal consistency: Cronbach α=0.96-0.99 Test-retest reliability: ICC^c^=0.85 Convergent validity with the Brief Pain Inventory: r=0.80-0.85
Physical function									
	PROMIS^b^-Physical Function Short Form 6b					Assesses the broader influence of pain on life domains, with raw scores ranging from 6 to 30; each item is scored from 1 (“unable to do”) to 5 (“without any difficulty”). Converted T-scores (mean 50, SD 10) range approximately from 20 to >80. T-scores >45 are within normal limits, scores from 40 to 45 suggest mild limitation, scores from 30 to 40 indicate moderate limitation, and scores <30 reflect severe limitation [29-31].		Internal consistency: Cronbach α=0.96 for person and 0.99 for item Construct validity: r=0.657 (in patients undergoing foot and ankle surgery)	
	FAAM^d^				Provides targeted assessment of foot and ankle function across two subscales: (1) activities of daily living (ADL), which includes 21 items scored from 0 (“unable to do”) to 4 (“no difficulty”), with a total score range of 0-84; and (2) sports, which includes 8 items with a total score range of 0-32. Scores are converted to percentages, with higher percentages reflecting better function [32].				Test-retest reliability: ICC=0.89 for the ADL; ICC=0.87 for the Sports. Correlations with the SF-36 physical function subscale: r=0.84-0.78 and physical component summary score: r=0.78-0.80
	VISA-A Sedentary^e^			Evaluates the severity of Achilles tendinopathy in sedentary individuals. It consists of 8 variably scored items addressing symptoms and activity impact, with a total score ranging from 0 to 100. A score of 100 indicates full function without symptoms, whereas scores <70 suggest notable impairment [33].					Test–retest reliability: ICC=0.991 for symptom and ICC=0.999 for activity Internal consistency: Cronbach α=0.72 Construct validity: r=0.42 for symptoms; r=0.40 for activity
